#### Calculation Hypotheses for the Number of Subjects Required and Result

The MDP-A1 subscale of the Multidimensional Dyspnea Profile is the main evaluation criterion of this study. This subscale is similar to the visual analog scale. Assuming a difference of 1 (on the primary efficacy endpoint, superiority study) between one of the 2 experimental groups and the placebo group and a standard deviation of 1, with a first species risk (alpha risk) of 2.5% (to take into account the 2 comparisons of each experimental group with placebo) and a power of 80% (beta risk at 20%), it will be necessary to include 21 patients per group or 63 patients in total. This number is consistent with that of other studies in tDCS (29, 60, 61).

The main analysis will be carried out according to the intention to treat principle. Only patients who have withdrawn their consent can be excluded from the analysis. If the period of inclusion in the research is still active, patients who have withdrawn their consent will be replaced. Patients who have decided to discontinue treatment planned in the trial, lost to follow-up or discontinued from the trial will be replaced, as will patients for whom there have been technical problems. Analyzes will be carried out with the intention of treating. Regarding missing data issue, in case of patient drop-out, in order to clearly understanding of the effectiveness of the therapy, we will first report results based on the completed cases, then secondarily with mixed-model or similar approaches which take into account partially available data, and finally with multiple imputation techniques.

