### Experimental Design

#### Randomization

After verification of the inclusion and exclusion criteria, the patients will be prospectively and randomly included in three groups of 21 patients, depending on the type of tDCS treatment received: anodal tDCS group, cathodal tDCS group, and placebo tDCS group. The tDCS will be applied up on the cortical representation zone of the primary motor and left pre-motor cortex for 30 min; intensity 2 mA (in anodal, cathodal, or placebo modality). The patient will be blinded from the randomization arm. Randomization will be performed on a dedicated and secure specific website (Cleanweb). Randomization will be carried out in a 1: 1: 1 ratio with permutation blocks of size unknown to the investigators.

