### Statistical Analysis

#### Descriptive Analysis

A descriptive analysis of inclusions and monitoring of the protocol will be carried out. The main analysis will be carried out according to the intention to treat principle. Only patients who have withdrawn their consent can be excluded from the analysis. Patients who have decided to discontinue the management planned for the trial, lost to follow-up, or discontinued the trial will be included in the analysis. In general, the quantitative variables will be described by their median and their first and their third quartiles and the qualitative variables will be described by the frequencies of the modalities and the associated percentages. The epidemiological and clinical characteristics of the patients at inclusion will be described by group, without statistical tests being carried out. The protocol violations, the causes of abandonment and loss of sight and the characteristics of these patients will be detailed.

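### Replacing stopped, lost or technically failed patients and reporting completed cases first conflicts with the stated intention-to-treat rule, leaving the primary comparison open to bias in either direction

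*Protocol article*

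**What the plan says.** Two sections of the protocol article govern who is counted.

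- **Descriptive Analysis.** The main analysis follows intention to treat, and withdrawal of consent is the only ground for exclusion. It adds: "Patients who have decided to discontinue the management planned for the trial, lost to follow-up, or discontinued the trial will be included in the analysis".
- **Calculation Hypotheses for the Number of Subjects Required and Result.** The intention-to-treat rule and the single ground for exclusion are repeated. Then comes: "Patients who have decided to discontinue treatment planned in the trial, lost to follow-up or discontinued from the trial will be replaced", extended to patients with technical problems, and after it another statement that analysis is by intention to treat. For missing data after drop-out, "we will first report results based on the completed cases", with mixed models second and multiple imputation last.

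The sample size is fixed in the same section: "it will be necessary to include 21 patients per group or 63 patients in total". It contains no allowance for loss.

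**The concern.** Take a randomised patient who has not withdrawn consent but has no post-session MDP-A1 score. Under Descriptive Analysis this patient is in the main analysis. Under the sample-size section the patient is replaced and is absent from the result reported first. The text does not say whether the replaced patient's data are kept, how the replacement is assigned to an arm, or what counts as a technical problem.

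If replaced patients are dropped, the groups compared are no longer those that were randomised. That matters when loss depends on both arm and response. The design makes this plausible: Description of the Acts Performed and Devices Used gives 30 minutes of current in the active arms and 2 minutes in sham. The trial is also single-blind. The patient and the primary-endpoint assessor are blinded, but nothing says that the person running the stimulator is. A technical problem could therefore be declared by someone who knows the arm.

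**Working it through.** **1. The plan's own sample size.** Inputs from the sample-size section: difference 1, SD 1, alpha 0.025 per comparison, power 80%. Allocation, from Randomization: "Randomization will be carried out in a 1: 1: 1 ratio".

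- Normal approximation, two-sided: n = 2 × (2.241 + 0.842)² = 19.0, rounded up to 20 per group.
- Exact t calculation, two-sided: 21 per group, with power 81.5%.
- One-sided 0.025 would give 16 (normal) or 17 (t).

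So 21 is reproduced as a two-sided 0.025 test. The chance of a false positive in favour of tDCS is nominally 0.025 / 2 = 1.25% per comparison.

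**2. The rules side by side**, for a consenting patient without a post-session score:

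| Rule | Consequence |
|---|---|
| Only consent withdrawals excluded (both sections) | In the analysis |
| Stopped or lost patients included (Descriptive Analysis) | In the analysis |
| Stopped, lost or technical-problem patients replaced (sample-size section) | Another patient enters; fate of this patient's data not stated |
| Completed cases reported first (sample-size section) | Not in the first result |

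The first two rows cannot be met by the result in the last row.

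**3. Possible size if replaced patients are dropped.** The documents give no loss rate, so the rates below are assumptions. Relief is the fall in MDP-A1. There is no true effect, SD is 1, and there are 21 per arm after replacement.

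*Shift model.* A share d of one active arm is lost, and their mean relief is g points below that of completers. The completer comparison shifts by d × g. The noncentrality is d × g × √(21/2) = 3.24 × d × g, referred to t with 40 degrees of freedom.

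| d | g | Shift toward tDCS | False positives favouring tDCS |
|---|---|---|---|
| 5% | 1 | 0.05 | 1.9% |
| 10% | 1 | 0.10 | 2.7% |
| 20% | 1 | 0.20 | 5.3% |
| 10%, poor responders lost from sham instead | 1 | −0.10 | 0.5% |
| Equal loss unrelated to outcome | – | 0 | 1.25% |

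*Worst case.* The lost patients are exactly the worst responders of one active arm. For a normal outcome the shift is φ(z) / (1 − f), where f is the share lost and z its normal quantile:

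- f = 10%: 0.1755 / 0.90 = 0.195 points
- f = 15%: 0.2332 / 0.85 = 0.274 points
- f = 20%: 0.2800 / 0.80 = 0.350 points

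Simulated false positives favouring tDCS are about 5%, 9% and 15%. The planned effect is 1 point.

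**4. What a mixed model would recover.** The endpoint has one score before and one after. In simulation with the worst 20% of one active arm lacking the second score, a baseline-adjusted likelihood analysis reduced the spurious benefit only from 0.35 to about 0.24–0.30 points. This assumes a pre–post correlation of 0.3 to 0.7.

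**The case against.** Replacement is not exclusion. The sentence straight after the replacement rule restates intention to treat, and Descriptive Analysis says that discontinued and lost patients are included. The sections can be read together as extra recruitment with the original patients retained. That reading is open. A reader might infer that the plan is a per-protocol analysis under an intention-to-treat label, but the text never says that replaced patients' data are discarded, so the inference goes too far.

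A reader might also infer that completed cases are the declared primary analysis. The text gives only an order of reporting, to be used if there is drop-out, and it twice calls the main analysis intention-to-treat. Mixed models and multiple imputation are both planned.

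Exposure may also be small. The primary endpoint is read 30 minutes after a single bedside session of about 90 minutes, so much of any loss would come later and affect only the day-28 outcomes. Finally, the trial describes itself as a pilot.

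All of this limits the size of the problem. It does not remove the conflict over a consenting patient without a post-session score, or the silence on what happens to replaced patients' data.

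**Conclusion.** The conflict is in the text and concerns who is counted in the primary comparison, so it should be resolved before any analysis. It is not a detail left to a fuller document, because the article itself fixes the intention-to-treat rule, the replacement rule and the order of reporting.

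Bias is possible, not demonstrated. It requires that replaced patients are dropped and that losses differ by arm and relate to response. If those losses fall on poor responders in one active arm, false positives favouring tDCS lie between about 1.9% (5% lost, 1 point worse than completers) and about 15% (the worst 20% lost), against 1.25%. The upper figure is a deliberate worst case. A reader might conclude that the plan favours tDCS, but the documents do not support a direction: loss of poor responders from sham reverses the shift, and equal loss unrelated to outcome produces none.

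**What to change.** Reconcile the two sections with four statements:

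1. Any patient added after a loss is newly randomised and displaces no one.
2. All randomised patients except consent withdrawals are analysed in their allocated arm, including those with technical problems.
3. The post-session MDP-A1 rating is still taken when stimulation was shortened or stopped.
4. The primary result is the analysis of all randomised patients, with completed cases as a sensitivity analysis.

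The third is the main safeguard, because a mixed model adds little for a patient with only a baseline score.

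The cost is wording plus a small loss of power if outcomes are missing: 81.5% with 21 per arm, 79.3% with 20, 76.8% with 19. If the sponsor wants 21 outcomes per arm, an enrolment allowance of 21 / (1 − loss rate) can take the place of replacement. An assumed 5% loss gives 21 / 0.95 = 22.1, so 23 per arm (69 in total); 10% gives 21 / 0.90 = 23.3, so 24 per arm (72 in total).

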## Ethical and Legal Aspects

This study was approved by our legal ethical committee: Comité de Protection des Personnes Ouest III, Université de Poitiers; CPP number 170946 and renewed on april 28th 2020. Informed consent should be obtained from each patient or family member before inclusion in the study.

## Conclusions

Dyspnea is a painful suffering that often reaches unbearable limits. Unfortunately, it is very frequent in intensive care and constitutes a major factor affecting the prognosis of intensive care patients, and more particularly patients under mechanical ventilation. Many COVID-19 patients continue to suffer from it, despite being put on mechanical ventilation and the use of relaxing and analgesic drugs (40). The effectiveness of the treatments currently available therefore remains very limited and there is a pressing need to develop other innovative treatments, including non- medicinal ones, in order to combat this scourge even more effectively and reduce the suffering of patients (39). The tDCS has demonstrated efficacy in pain relief, which shares the same neural substrates as dyspnea. It is a painless, easy to use and non-invasive technique. The originality and the innovative character of this study reside in the development of an effective method of treatment by neuro-modulation non-invasive and easy to use to combat this respiratory suffering in COVID-19 patient. Effective relief of dyspnea with tDCS would also have a significant impact on the prognosis of these patients. Finally, one may argue that it could have been better to conduct a multisession tDCS study, however this study is a pilot, designed to assess whether a single 30 min tDCS session could be beneficial for dyspnea relief in this specific patients' population. According to the findings of the present study we will conceive and assess outcome of other tDCS treatment strategies and designs including multisession ones.
